### Power and Analytic Plan

Table 2 describes the study power to assess noninferiority across multiple primary outcomes, priority secondary outcomes, and other secondary outcomes at 3 months after treatment.

**Table 2 table2:** Noninferiority margin and power.

Outcome		Time point	NM^a^ (SD for 3-month change)	NM in terms of the baseline (SD of the NM)	Power (%)
**Multiple primary outcomes**					
	Pain intensity	Month 3	2.8 (7.7) [60]	0.21 (7.3)	69
	Pain interference^b^	Month 3	4.5 (7.9) [39]	0.47 (6.4)	96

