### Inclusion and Exclusion Criteria

Inclusion criteria are age ≥18 years, receipt of medical care through a Lupus PROGRESS study site, experience of chronic pain for 3 or more months with past-month average severity of 3 or more on a 10-point scale [23], and diagnosis of SLE. To enhance SLE diagnostic accuracy, we are applying criteria based on the work by Falasinnu et al [23] to increase the likelihood of true idiopathic SLE rather than drug-induced lupus or other secondary lupus conditions more common in older adults and to align with typical SLE onset and disease patterns. Patients must be actively and continuously enrolled in a commercial or Medicare Advantage plan for at least 6 months to ensure that all outcome measures are available. Following the work by Falasinnu et al [3], patients are required to have 2 or more lupus diagnostic codes from Textbox 1 on different dates separated by 7 to 365 days during the data period, with at least one code from a rheumatologist, dermatologist, or nephrologist. Per Humana institutional policies, members enrolled in administrative services–only insurance, Medicaid, and other research-excluded groups will be excluded. Other exclusion criteria are inability to consent, complete study measures (online or paper based), or participate in internet-based treatment groups. Past-3-month receipt of Empowered Relief or CBT and active suicidal ideation at screening are also exclusionary. Concomitant pain care of other types is allowed, self-reported throughout the trial, and will be reported in the study.

Lupus International Classification of Diseases codes (2 required for eligibility).M32.9: systemic lupus erythematosus, unspecifiedM32.10: systemic lupus erythematosus, organ or system involvement unspecifiedM32.11-M32.15: systemic lupus erythematosus, specific to organ involvementM32.19: systemic lupus erythematosus, other organ or system involvement M32.8: other forms of systemic lupus erythematosus

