### Study Measures

Self-reported demographic data are collected at baseline and include age, gender identity, sex at birth, race and ethnicity, household composition, educational attainment, veteran status, disability status, employment status, annual household income, and pregnancy status. Additional baseline variables include pain history, prior behavioral pain treatment, current pain treatments, and barriers to pain care. Substance use is assessed using the National Institute on Drug Abuse 4-item quick screen, pain distribution is assessed using the Stanford CHOIR visual body map [31], treatment expectancy is assessed after treatment assignment is revealed to participant using the 6-item Stanford Expectations of Treatment Scale [32], and immediately after treatment, satisfaction and perceived utility are assessed using study-specific items [9].

Participants complete validated measures at baseline; immediately before treatment; and at 1, 2, 3, and 6 months after treatment, with Table 1 showing each outcome, the specific measure used, and the time points of administration. Additional posttreatment measures include treatment burden and satisfaction; engagement is assessed via session attendance. Health care use is evaluated using electronic medical record or claims data comparing the 3 months prior to enrollment with the final 3 months of follow-up.

**Table 1 table1:** Primary, priority secondary, other secondary, and exploratory outcomes.

Outcome type	Name of outcome	Specific measure to be used	Time points
Multiple primary	Pain intensity	Numeric rating scale (0-10) [33-36]	Baseline; immediately before treatment^a^; and months 1, 2, 3, and 6 after treatment
Multiple primary	Pain interference	PROMIS^b^ 6-item Pain Interference scale [36-41]	Baseline; immediately before treatment; and months 1, 2, 3, and 6 after treatment
Priority secondary	Sleep disturbance	PROMIS 6-item Sleep Disturbance scale [42]	Baseline; immediately before treatment; and months 1, 2, 3, and 6 after treatment
Priority secondary	Pain bothersomeness	Numeric rating scale (0-10)	Baseline; immediately before treatment; and months 1, 2, 3, and 6 after treatment
Priority secondary	Pain catastrophizing	Pain Catastrophizing Scale (13 items) [43,44]	Baseline; immediately before treatment; and months 1, 2, 3, and 6 after treatment
Priority secondary	Anxiety	PROMIS 6-item Anxiety scale [45-47]	Baseline; immediately before treatment; and months 1, 2, 3, and 6 after treatment

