**Priority secondary outcomes**					
	Sleep disturbance^b^	Month 3	4.0 (6.2) [61]	0.16 (9.3)	99
	Pain bothersomeness	Month 3	1.5 (2.2) [62]	0.68 (2.2)	>99
	Pain catastrophizing	Month 3	6.8 (9.8) [63]	0.35 (11.3)	>99
	Anxiety^b^	Month 3	3.0 (7.0) [64]	0.33 (9.1)	89

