**Exploratory outcomes**					
	Brief Index of Lupus Damage	Month 3	—^c^	—	—
	Systemic Lupus Activity Questionnaire	Month 3	—	—	—

^a^NM: noninferiority margin.

^b^These are Patient-Reported Outcomes Measurement Information System (PROMIS) measures that use T-scores (indicated by b; values represent <0.5 SD for each PROMIS variable).

^c^Not applicable.

The sample size of 75 patients per group was selected to support noninferiority testing for 2 primary outcomes (pain intensity and pain interference) at a 1-sided significance level of 10%/2=5%, and all secondary outcomes (sleep disturbance, pain bothersomeness, pain catastrophizing, anxiety, satisfaction with social roles and responsibilities, patient global impression of change, anger, fatigue, and depression) at a 1-sided significance level of 10%. Different significance levels were selected to account for multiple testing and reflecting the priority of the outcomes. Table 2 shows the power for the primary, priority secondary, and other secondary outcomes, with sufficient power (>70%) achieved for most outcomes except pain intensity, and satisfaction with roles and responsibilities; the study is not powered to detect changes in SLE-related activity and disease burden outcomes.

Primary analyses will evaluate the noninferiority of Empowered Relief compared with 8-session CBT for pain intensity and pain interference at 3 months after treatment based on estimated treatment effects from a mixed model for repeated measures (MMRM) with an unstructured covariance matrix under an intention-to-treat framework. We will conduct 2 separate MMRMs analyses for pain intensity and pain interference; for addressing missing data, MMRM is considered superior over other options such as multiple imputation or least observation carried forward. Specifically, treatment effects at month 3 will be estimated through the treatment-by-time interaction at the 3-month time point. Secondary analysis will similarly evaluate the noninferiority of Empowered Relief compared with CBT for 4 priority secondary outcomes and 5 other secondary outcomes at the month 3 visit. We will also evaluate the noninferiority of all the aforementioned outcomes at the month 6 visits. Exploratory analyses will evaluate within-group change trajectories and compare treatment completion, patient burden, and exploratory health care use outcomes between the 2 groups. Exploratory analyses will examine changes in the BILD and SLAQ for both groups.

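### The Table 2 row for the primary outcome pain intensity (margin 2.8, SDs 7.7 and 7.3, power 69%) does not fit the 0-10 scale on which Table 1 says it is measured

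*Protocol article*

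**What the plan says.** Study Measures, Table 1, defines the outcome: "Pain intensity Numeric rating scale (0-10". Pain bothersomeness is collected in the same format: "Pain bothersomeness Numeric rating scale (0-10". Entry requires "past-month average severity of 3 or more on a 10-point scale".

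In Power and Analytic Plan, the numeric columns of Table 2 are headed "NM^a^ (SD for 3-month change) NM in terms of the baseline (SD of the NM) Power". The two rows for 0-10 scales are:

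- Pain intensity (primary): "Pain intensity Month 3 2.8 (7.7) [60] 0.21 (7.3) 69"
- Pain bothersomeness (priority secondary): "Pain bothersomeness Month 3 1.5 (2.2) [62] 0.68 (2.2) >99"

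Footnote b marks the PROMIS rows as T-scores and adds that "values represent <0.5 SD for each PROMIS variable". Pain intensity does not carry it. The two primary outcomes are tested at one-sided 5% with 75 per arm.

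The text on power is mixed. The paragraph after Table 2 lists pain intensity as an exception to adequate power (above 70%). A later paragraph of the same section says that 150 participants give enough power for both primary outcomes. The Discussion says that three outcomes have less than 80%.

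**The concern.** The margin is the decision threshold for a primary outcome. Its row carries SDs of the size seen in the T-score rows, while the instrument is a 0-10 rating. If margin and SDs come from another metric, two things follow. The trial has no usable margin for the score it collects, and the stated power describes a variable it does not measure. If 2.8 were nevertheless applied to the 0-10 score, the test would tolerate a large disadvantage of the one-session arm. The printed ratio disagrees with the printed margin as well, so the row can be read as supporting two different thresholds.

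**Working it through.** **1. Reproduce the stated power.** Inputs from Table 2 and the text: margin 2.8, change SD 7.7, one-sided 5%, true difference 0. Power = Φ(margin / (SD × √(2/n)) − 1.645).

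- n = 75 per arm: standard error 7.7 × √(2/75) = 1.257; 2.8/1.257 = 2.227; power 72.0% (noncentral t 71.6%).
- n = 70 per arm: standard error 1.302; 2.8/1.302 = 2.151; power 69.4% (noncentral t 69.0%).

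The printed 69% therefore comes from 2.8 and 7.7 at about 70 per arm. That is roughly 7% attrition, which the article does not state. The same n of 70 fits all 11 powered rows. So 2.8 and 7.7 are the values used in the calculation, not a misprint in one cell.

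**2. Check the SDs against the scale.** The largest SD of a score confined to [a, b] is (b − a)/2, which is 5.0 for 0-10. The second SD, 7.3, exceeds it. For a change score, if every baseline is at least 3, change lies between −10 and +7 and its SD cannot exceed 8.5. So 7.7 is not strictly impossible, but it would need nearly everyone at opposite extremes. It is 7.7/2.2 = 3.5 times the figure for bothersomeness.

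**3. Is the second SD the baseline SD?** The header is unclear. Dividing the margin by the second SD gives the printed ratio in seven rows: bothersomeness (1.5/2.2 = 0.68), anxiety (3.0/9.1 = 0.33), satisfaction with roles (2.0/8.0 = 0.25), global impression of change (0.5/1.5 = 0.33), depression (3.0/10.4 = 0.29), fatigue (4.0/9.3 = 0.43) and anger (5.0/11.6 = 0.43). That supports the reading. Four rows fail:

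| Row | Margin / second SD | Printed ratio | Printed ratio × second SD |
|---|---|---|---|
| Pain intensity | 2.8/7.3 = 0.38 | 0.21 | 1.5 |
| Pain interference | 4.5/6.4 = 0.70 | 0.47 | 3.0 |
| Sleep disturbance | 4.0/9.3 = 0.43 | 0.16 | 1.5 |
| Pain catastrophizing | 6.8/11.3 = 0.60 | 0.35 | 4.0 |

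Both primary outcomes are among the four.

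**4. Consequence if 2.8 is used on the 0-10 score.** It is 2.8/10 = 28% of the scale and 2.8/1.5 = 1.9 times the bothersomeness margin. The article gives no change SD for pain intensity in points, so 2.0 to 3.0 is assumed, a range that includes the 2.2 for bothersomeness. With 75 per arm, one-sided 5% and a true deficit of 2.0 points, the chance of declaring noninferiority depends on (2.8 − 2.0)/(SD × √(2/75)). By noncentral t:

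| Assumed change SD | Chance of declaring noninferiority |
|---|---|
| 2.0 | 79% |
| 2.2 | 72% |
| 2.5 | 62% |
| 3.0 | 49% |

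At a true difference of 0, power with margin 2.8 is about 100% over this whole range, not 69%.

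**5. Power on the collected scale, for illustration only.** With 75 per arm, margin 1.5 gives 99.8% at SD 2.0, 99.4% at 2.2 and 92.2% at 3.0. Margin 1.0 gives 92.2% at SD 2.0 and 65.4% at 3.0.

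**The case against.** Several limits on the criticism stand.

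- A margin of 2.8 can be written on a 0-10 scale, and 7.7 is below the theoretical ceiling for a change score. Only 7.3 is impossible, and only if it is the baseline SD.
- One might tighten the bound on the baseline SD to 3.5 because entry requires 3 or more. That floor applies to past-month average severity at screening, and the baseline survey is a separate step. Only the bound of 5 is safe.
- A reader might describe 2.8 as almost all of the minimum entry pain (2.8/3 = 93%). That divides a between-group margin by the eligibility floor, and mean baseline pain will be higher. The neutral figure is 28% of the scale.
- A reader might infer that the right margin is 1.5, because bothersomeness uses it and 0.21 × 7.3 gives it. Bothersomeness is a different outcome with a different cited source, so the article does not establish this.
- A reader might infer that the pain interference margin breaks footnote b and must lie below 3.2 (half of 6.4). The footnote does not say which SD it means. If it means a T-score SD of 10, an assumption here, 4.5 is 0.45 SD and that row complies. With four faulty ratios, the fault may also lie in the column rather than in the margins.
- Low power for pain intensity is disclosed, and the statistical analysis plan may hold the correct figures.

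None of this reconciles the two tables. The point is not that something was left out: figures stated in the article cannot stand together, and nothing in it rescales pain intensity. Disclosing 69% does not help when that figure belongs to another metric.

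**Conclusion.** The point holds as a contradiction between Table 1 and the pain intensity row of Table 2. The row's SDs do not fit a 0-10 score, its ratio does not follow from its margin, and its 69% power was computed from figures that do not describe the outcome collected. Strict impossibility rests on reading 7.3 as the baseline SD, which seven of 11 rows support.

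The harm is conditional. If 2.8 is applied to the 0-10 score, a true 2.0-point disadvantage passes as noninferior about 79% to 49% of the time, for an assumed change SD of 2.0 to 3.0. The article does not settle which metric the figures came from or what the margin should be. For pain interference, the mismatch between 0.70 and 0.47 is certain, but which cell is wrong is not.

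**What to change.** Before unblinding:

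- Restate the pain intensity row on the 0-10 scale: a justified margin, the baseline SD and the change SD, all in points, with power recomputed and the number per arm it assumes stated. The bothersomeness margin of 1.5 is a reference point, not a prescribed value.
- Clarify the header of the second margin column. Correct the ratios for pain intensity, pain interference, sleep disturbance and pain catastrophizing, and state which SD footnote b refers to.
- For pain interference, confirm whether the margin is 4.5 or the 3.0 implied by 0.47 × 6.4. With 3.0, SD 7.9 and one-sided 5%, power would be about 75% at 75 per arm or 73% at 70, against the printed 96%.
- Reconcile the two statements on power for pain intensity in Power and Analytic Plan.

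No new patients are needed. But 130 of 150 were enrolled by May 2026, so a changed primary margin is more than a wording correction and should be documented with its rationale. The statisticians remain blinded until database lock, so this can still be done credibly.

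### Table 2: for four outcomes, including both primaries, the margin in baseline units does not agree with the raw margin in the same row

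*Protocol article*

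**What the plan says.** Table 2 (Methods, Power and Analytic Plan) has two margin columns and a power column. The first gives the raw margin with, in parentheses, the "SD for 3-month change". The second is headed "NM in terms of the baseline (SD of the NM") and gives a standardized value with a second SD.

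The affected rows include pain interference, "Month 3 4.5 (7.9) [39] 0.47 (6.4) 96", sleep disturbance, "Month 3 4.0 (6.2) [61] 0.16 (9.3) 99", and pain catastrophizing, "Pain catastrophizing Month 3 6.8 (9.8) [63] 0.35 (11.3"). The fourth is pain intensity: raw margin 2.8 (change SD 7.7), baseline-unit margin 0.21 (SD 7.3), power 69%.

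Footnote b says of the PROMIS rows that "values represent <0.5 SD for each PROMIS variable". It does not say which SD is meant.

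Below the table the article states: "The sample size of 75 patients per group was selected to support noninferiority testing for 2 primary outcomes". The one-sided level is 5% for the primary outcomes and 10% for all secondary outcomes.

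**The concern.** The two margin columns should describe one threshold in two units. In four rows they describe different thresholds, and two of those rows are the primary outcomes.

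In a noninferiority trial the margin is the decision rule. Suppose the upper confidence limit for pain interference came out at 3.8 T-score points. That is noninferior against 4.5 but not against the 3.0 that the baseline-unit column implies. A reader who judges the margin by its standardized size would think the interference threshold is 0.47 SD, when the raw figure beside it is 0.70 SD. If the choice between two published margins is made after unblinding, it can be challenged as post hoc.

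**Working it through.** **Inputs.** All margins, SDs and power figures are from Table 2. The 75 per arm and the one-sided levels (5% primary, 10% secondary) are from the text below it.

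**Step 1: how the baseline-unit column is built.** Try ratio = raw margin / SD printed in the baseline-unit column.

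| Outcome | Calculation | Result | Printed |
|---|---|---|---|
| Pain bothersomeness | 1.5/2.2 | 0.68 | 0.68 |
| Anxiety | 3.0/9.1 | 0.33 | 0.33 |
| Satisfaction with roles | 2.0/8.0 | 0.25 | 0.25 |
| Global impression of change | 0.5/1.5 | 0.33 | 0.33 |
| Depression | 3.0/10.4 | 0.29 | 0.29 |
| Fatigue | 4.0/9.3 | 0.43 | 0.43 |
| Anger | 5.0/11.6 | 0.43 | 0.43 |
| **Pain intensity** | 2.8/7.3 | **0.38** | **0.21** |
| **Pain interference** | 4.5/6.4 | **0.70** | **0.47** |
| **Sleep disturbance** | 4.0/9.3 | **0.43** | **0.16** |
| **Pain catastrophizing** | 6.8/11.3 | **0.60** | **0.35** |

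Seven rows reproduce. Anxiety and depression show that the change SD is not the divisor: it would give 3.0/7.0 = 0.43 and 3.0/7.6 = 0.39.

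**Step 2: can the four gaps be explained?**
- Rounding: with ±0.05 on both inputs the possible ranges are 0.374–0.393 (intensity), 0.690–0.717 (interference), 0.422–0.438 (sleep) and 0.595–0.609 (catastrophizing). None reaches the printed value.
- Change SD as divisor: 2.8/7.7 = 0.36, 4.5/7.9 = 0.57, 4.0/6.2 = 0.65, 6.8/9.8 = 0.69. None matches.
- Without assuming any formula: sleep and fatigue have the same raw margin (4.0) and the same baseline-unit SD (9.3), yet show 0.16 and 0.43.

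**Step 3: what margins do the printed ratios imply?** Margin = ratio × SD:
- intensity 0.21 × 7.3 = 1.53
- interference 0.47 × 6.4 = 3.01
- sleep 0.16 × 9.3 = 1.49
- catastrophizing 0.35 × 11.3 = 3.96

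Raw margin over implied margin is 1.83, 1.50, 2.69 and 1.72.

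**Step 4: which margin does the power column use?** Power = Φ(M/(s√(2/n)) − z), with true difference 0, s the change SD, z = 1.645 (5%) or 1.282 (10%). For interference at n = 75: 7.9 × √(2/75) = 1.290; 4.5/1.290 = 3.488; Φ(3.488 − 1.645) = 96.7%.

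| Outcome | Printed | Raw margin, n = 75 | Raw margin, n = 70 | Implied margin, n = 75 |
|---|---|---|---|---|
| Pain intensity | 69 | 72.0 | 69.4 | 33.5 |
| Pain interference | 96 | 96.7 | 95.8 | 75.4 |
| Sleep disturbance | 99 | 99.6 | 99.4 | 57.5 |
| Pain catastrophizing | >99 | 99.8 | 99.8 | 88.3 |

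The printed power goes with the raw margins and change SDs. At 75 per arm it comes within about 3 points in every row. At about 70 per arm, a value fitted here and not stated in the article, all eleven rows agree within 1 point. The implied margins do not give the printed power in any of the four rows.

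**Step 5: footnote b.** For pain interference, 4.5/6.4 = 0.70 and 4.5/7.9 = 0.57, both above 0.5. On an assumed T-score reference SD of 10, which the article does not state, 4.5/10 = 0.45 would satisfy it, but anger at 5.0/10 = 0.50 would not be below 0.5.

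**Step 6: pain intensity scale.** Table 1 gives pain intensity as a 0-10 numeric rating. The largest population SD on such a scale is 5 (half the scores at 0, half at 10). A baseline SD of 7.3 is therefore impossible on it, and the 0.38 for this row is only internal to the printed numbers.

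**The case against.** The strongest reply is that the raw margins are plainly the operative ones. Their column is the one headed as the noninferiority margin, and the power column follows it in every row. On that view the baseline-unit column is descriptive and merely misprinted. Most of this stands, and it makes the baseline-unit column the likelier error. It does not close the matter. The text never says which column governs, and the implied values lie close to round numbers (1.5, 3.0, 1.5, 4.0), which could mean a second set of margins. That last point is inference.

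The column header is also loose: it calls the bracketed figure the SD of the margin. Reading it as a baseline SD is an inference, though seven rows support it, and the sleep-fatigue conflict does not depend on it.

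On footnote b, the defence is that it names no SD and may mean the T-score reference. A reader might call the footnote simply false; the article does not support anything that absolute. What can be said is that it fails for pain interference on both SDs printed in that row. A reader might also extend the failure to sleep disturbance from its change SD (0.65). The footnote does not name that SD, and on the baseline-unit SD sleep is 0.43 and satisfies it. Every PROMIS value printed in the baseline-unit column is below 0.5 (maximum 0.47), so the footnote may simply carry over the same error.

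An unseen SAP does not answer the point, because the conflicting figures stand in the same printed rows.

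**Conclusion.** Table 2 is internally inconsistent for pain intensity, pain interference, sleep disturbance and pain catastrophizing. Raw and implied margins differ by factors of 1.5 to 2.7.

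Two stronger conclusions are tempting and not supported. One is that the true margins are shown 1.5 to 2.7 times too tight; that takes the raw margins as governing, which is likely but unstated. The other is that the trial has only about 34% and 75% power on its primaries; that holds only if the smaller margins were intended. In that case interference and sleep would also fall below 80%, making five outcomes instead of the three acknowledged in the Discussion.

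Nor can 0.38 SD be presented as what the trial rules out for pain intensity, since the SD behind it does not fit the stated scale.

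The ratios rest only on printed figures. The power figures assume a true difference of 0, the printed change SDs and 75 analysed per arm.

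**What to change.** Before unblinding, confirm one margin per outcome and state that it governs.
- If the raw margins stand, correct the baseline-unit values to 0.70 (pain interference), 0.43 (sleep disturbance) and 0.60 (pain catastrophizing).
- If the baseline-unit values stand, restate the raw margins for these three (about 3.0, 1.5 and 4.0) and the lower power (about 75%, 58% and 88% at 75 per arm).
- For pain intensity, first reconcile the scale with Table 1, then restate margin, both SDs, ratio (0.38 on the printed raw figures) and power on the scale actually used.
- Name the SD that footnote b uses, or drop the claim for pain interference. If a reference SD of 10 is named, the anger margin still needs different wording.

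The cost is a correction to one table and its footnote, and to any SAP that repeats them. The downside is that either the margins or the power will look less favourable. There is time: enrollment was still open in May 2026 and statisticians stay blinded until database lock.
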